## 6. Study process

| Item observed                                             |               | Screening /
baseline period             | Treatment period |                    |                     | Follow-up period    |                     |
|-----------------------------------------------------------|---------------|--------------------------------------------|------------------|--------------------|---------------------|---------------------|---------------------|
|                                                           |               | Visit 1
From onset to the
first dose | The first dose   | Visit 2
Day 7±1 | Visit 3
Day 14+3 | Visit 4
Day 30±7 | Visit 5
Day 90±7 |
| Informed consent                                          |               | X                                          |                  |                    |                     |                     |                     |
| Collection of demographics and
disease characteristics |               | X                                          |                  |                    |                     |                     |                     |
| Past medical history and
medication history            |               | X                                          |                  |                    |                     |                     |                     |
| Evaluation of the
inclusion/exclusion criteria         |               | X                                          |                  |                    |                     |                     |                     |
| Vital signs and physical
examination                   |               | X                                          |                  | X                  | X                   | X                   | X                   |
| Laboratory
and auxiliary                               | Blood routine | X                                          |                  | X                  | X                   | X                   | X                   |
|                                                           | Urine routine | X                                          |                  | X                  | X                   | X                   | X                   |

|              |                            |                  |  |   |   |   |                  |
|--------------|----------------------------|------------------|--|---|---|---|------------------|
| examinations | Hepatic and renal function | X  |  | X | X | X | X                |
|              | Myocardial enzyme          | X                |  | X | X | X | X                |
|              | Electrolytes               | X                |  | X | X | X | X                |
|              | Fasting blood glucose      | X  |  | X | X | X | X                |
|              | Blood lipid                | X                |  | X | X | X | X                |
|              | Coagulation function       | X                |  | X | X | X | X                |
|              | Homocysteine               | X                |  | X | X | X | X                |
|              | Electrocardiogram          | X                |  | X | X | X | X                |
|              | Pregnancy test             | X  |  |   |   |   | X  |
|              | Cranial CT                 | X                |  |   |   |   |                  |
|              | Cranial MRI                | X  |  |   |   |   |                  |
| Score        | mRS score                  | X  |  |   | X | X | X                |
|              | NIHSS score                | X                |  |   | X | X | X                |

|                                |                  |                  |   |   |  |  |
|--------------------------------|------------------|------------------|---|---|--|--|
| Parallel exploratory biomarker | X                |                  | X | X |  |  |
| SSS TOAST classification       |                  | X  |   |   |  |  |
| Randomization                  | X                |                  |   |   |  |  |
| Dosing                         |                  | X  |   |   |  |  |
| Concomitant medication         | X  |                  |   |   |  |  |
| Adverse event assessment       | X  |                  |   |   |  |  |

[1] Results of ALT, AST, and serum creatinine need to be obtained prior to randomization.

[2] Non-fasting state is allowed in the tests prior to treatment, indicating whether it's fasting or not.

[3] For women of childbearing age only.

[4] Optional and completed during the study. It is not a protocol deviation when the subject is unable to complete the MRI due to his/her own reasons.

[5] mRS score before this onset.

[6] Completion after SSS TOAST classification and enrolling is acceptable.

[7] Use as soon as possible after randomization.

[8] Concomitant medications and adverse events should be recorded from the time of signing the informed consent form to Day 90 of medication or the last follow-up.

If adverse event occurs, the subject will be followed up until the adverse event disappears or is restored to baseline levels or is not clinically significant.

**6.1. Screening period (visit 1)**

- Informed consent form
- Demographics, including age, gender, height and weight (Height and weight information of subjects with unfavorable limbs can be obtained through interrogation);
- Disease attributes;
- Past medical history and medication, disease history and medication history before enrollment;
- Vital signs and physical examination, including heart rate, blood pressure, body temperature and respiratory rate. Physical examination is evaluated by organ and system;
- Blood routine, blood biochemistry (hepatic and renal function, blood glucose (non-fasting), blood lipids, myocardial enzyme, electrolytes and homocysteine), urine routine, coagulation function and ECG examination;
- Pregnancy test (for women of childbearing age only);
- NIHSS score; (If thrombolysis subjects have completed the NIHSS for screening period before thrombolysis, the pre-thrombolysis score should be used as the basis for enrollment)
- mRS score before this onset;
- Cranial CT (plain scan);
- Cranial MRI (optional and completed during the study);
- Randomization.

**6.2. Treatment period****6.2.1. D7 ( $\pm 1$ ) (visit 2)**

- Vital signs and physical examination (including weight)
- Blood routine, blood biochemistry (Hepatic and renal function, blood glucose (fasting), blood lipids, myocardial enzyme, electrolytes and homocysteine), urine routine, coagulation function and ECG examination

**6.2.2. D14 (+3) (visit 3)**

- Vital signs and physical examination (including weight)
- Blood routine, blood biochemistry (Hepatic and renal function, blood glucose (fasting), blood lipids, myocardial enzyme, electrolytes and homocysteine), urine routine, coagulation function and ECG examination
- NIHSS score
- mRS score

Note: If the last medication is on Day 15, visit 3 shall be on D15+3

**6.3. Follow-up period****6.3.1. D30 ( $\pm 7$ ) (visit 4)**

- Vital signs and physical examination (including weight)
- Blood routine, blood biochemistry (Hepatic and renal function, blood glucose (fasting), blood lipids, myocardial enzyme, electrolytes and homocysteine), urine routine, coagulation function and ECG examination
- NIHSS score
- mRS score

**6.3.2. D90 ( $\pm 7$ ) (visit 5)**

- Vital signs and physical examination (including weight)
- Blood routine, blood biochemistry (Hepatic and renal function, blood glucose (fasting), blood lipids, myocardial enzyme, electrolytes and homocysteine), urine routine, coagulation function and ECG examination
- NIHSS score
- mRS score
- SSS TOAST classification (to be completed during the trail period after enrollment)

Note: For subjects who drop out in the midway, they should try to complete the visit (withdrawal visit) according to the requirements of visit 5.

At sites participating in the research of exploratory indicator biomarkers, a tube of venous blood (about 4mL) should be sampled from the subject before the first administration and on Day 7 ( $\pm 1$ ) (and Day 14 (+3)) after the administration, and send it to the unified

laboratory for testing. See Section 2.2.4 for specific indicators.

### 6.3.3. Follow-up endpoint

All subjects who have been treated with investigational product need to be followed up until:

1. Visit 5 has been completed according to the proposal;
2. Subjects died during follow-up period;
3. Serious violation of the inclusion and exclusion criteria is found after enrollment, and both the investigator and the Sponsor think the follow-up visit needs to be discontinued;
4. If the subject withdrew from the study midway (see Section 5.7.1 for Reasons for withdrawal), the time of the last evaluation shall be the follow-up endpoint. If the subject withdrew due to intolerable adverse reactions, the follow-up visit shall be carried out according to Section 7.3.

## 7. Study measures

### 7.1. Efficacy measures

- For the overall outcome scale, it is assessed by the Modified Rankin Scale (mRS), which measures the global disability. See Appendix 2 for details.
- Neurological Disability Score (NDS) scale  
See Appendix 3 for the NIH Stroke Scale (NIHSS).

### 7.2. Safety measures

#### 7.2.1. Safety evaluation indexes

- Vital signs and physical examination, including heart rate, blood pressure, body temperature and respiratory rate. Physical examination is evaluated by organ and system;
- Laboratory test, including blood routine, urine routine (qualitative or quantitative), blood biochemistry (including hepatic and renal function, blood glucose, blood lipids, myocardial enzyme, electrolyte), coagulation function, electrocardiogram, pregnancy test (women of childbearing age). See Table 7.2- 1 for detailed test items

**Table 7.2- 1: Laboratory test items and observation indicators**

| Laboratory item | Requirement and observation indicator |
|-----------------|---------------------------------------|
|-----------------|---------------------------------------|

|                       |                            |                                                                                                                                                |
|-----------------------|----------------------------|------------------------------------------------------------------------------------------------------------------------------------------------|
| Blood routine         |                            | White blood cell count, neutrophil count, lymphocyte count, hemoglobin, platelet                                                               |
| Blood
biochemistry | Hepatic and renal function | Alanine transaminase (ALT), aspartate aminotransferase (AST), alkaline phosphatase (ALP), TBil, DBil, creatinine, urea, total protein, albumin |
|                       | Blood glucose              | Determination of serum glucose                                                                                                                 |
|                       | Blood lipid                | Total cholesterol, triglyceride                                                                                                                |
|                       | Myocardial enzyme          | Creatine Kinase (CK), CK-MB, Lactate dehydrogenase (LDH)                                                                                       |
|                       | Electrolytes               | Serum potassium, serum sodium and serum chlorine                                                                                               |
|                       | Others                     | Homocysteine                                                                                                                                   |
| Coagulation function  |                            | Prothrombin time (PT), Activated partial thromboplastin time (APTT), International normalized ratio (INR), Fibrinogen (FIB)                    |
| Urine routine         |                            | Leukocyte, protein, glucose, ketone bodies, occult blood                                                                                       |
| Electrocardiogram     |                            | Standard 12-lead ECG or above                                                                                                                  |
| Pregnancy test        |                            | Blood or urine HCG pregnancy test                                                                                                              |

### 7.2.2. Laboratory test and evaluation on safety

This study received laboratory data from various sites.

The specific laboratory parameters included in each set of laboratory test (for example, hematology, biochemical tests and urine analysis) are determined by the site and implemented according to the corresponding SOP.

- The investigator must review the laboratory report, record the evaluation and record any clinically relevant changes during the study in the AE section of the case report form (CRF). The laboratory report must be filed with the source file.
- If a non-protocol laboratory evaluation conducted in a local laboratory of the institution results in a change of the subject management procedures or such change

is deemed clinically significant by the investigator (for example, SAE or AE or dose change), the results must be recorded in the corresponding CRF.

- Any laboratory abnormality with clinical significance should be repeatedly evaluated as much as possible until all serious adverse events on test value, and adverse events related to the study or making the subject stop the study treatment are followed up until the event is cured (including returning to the baseline value), and the subject's status changes to long-term stability, the subject is lost to follow-up or died.

### **7.3. Safety report and evaluation**

During the study, the investigator and his/her designated qualified personnel are responsible for detecting and recording all events observed during the study that meet the definition of adverse events or serious adverse events according to the standards and definitions specified in the protocol. The investigator should evaluate the adverse events, monitor the safety status of subjects and take corresponding protective measures to ensure the safety of subjects, and report according to relevant requirements.

#### **7.3.1. Definition of adverse event, serious adverse event and suspected unexpected serious adverse event**

Adverse Event (AE) refers to all adverse medical events that occur after the subject receives the investigational product, but not necessarily have causal relationship with the investigational product. It can be manifested as symptoms, signs, diseases or laboratory abnormalities. Therefore, AEs may be any adverse, unintentional physical sign (including abnormal laboratory results), symptom or disease (new or worsening) that is chronologically associated with the use of a certain study drug.

#### **Events that meet the definition of adverse events include:**

- Abnormal laboratory test results (hematology, clinical biochemistry or urine analysis) or other safety evaluations (such as ECG, radiological scan, vital sign measurement), including those that are deteriorated relatively to the baseline and are considered clinically significant according to the medical and scientific judgment of the investigator (that is, it's not related to the progress of underlying diseases).

- The deterioration of preexisting diseases, including the increase in the frequency and/or severity of the diseases.
- New symptoms detected or diagnosed after starting the administration of investigational product (even if they may already exist before the study starts).
- Signs, symptoms or clinical sequelae of suspected drug - drug interaction.

**Events that do not meet the definition of adverse events include:**

- Abnormal laboratory results or other abnormal safety evaluations related to underlying diseases. However, if the investigator believes that the severity is beyond the expected level based on the condition of the subject, it should be considered as an AE.
- The disease under study, or the expected progress, signs or symptoms of the disease under study. However, if the severity is beyond the expected level based on the subject's condition, it shall be considered as an AE.
- Medical or surgical operations (such as endoscopy, appendectomy). Please note that the disease causing such operation is an AE.
- There are no adverse events (hospitalization for social reasons and/or for convenience).
- The underlying disease or condition existing or detected at the beginning of the study is not deteriorated obviously with daily fluctuation within the expected range.
- Existing diseases or signs and/or symptoms not related to the study before the first trial medication. These events should be recorded in the medical history section of eCRFs.

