**2.2.3. Safety outcomes**

- Incidence of adverse events (AEs) in each group;
- Incidence of treatment-related adverse events (TEAEs) in each group;
- Changes in vital signs and laboratory data in each group before and after treatment.

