**Definition of serious adverse event**

Serious Adverse Event (SAE) refers to an adverse medical occurrence in subjects, such as death, life threatening, permanent or serious disability or loss of function, hospitalization required or prolonged hospitalization, congenital abnormalities or birth defects, etc., after receiving the investigational product.

- Result in death
- Life-threatening

It means that the subject is already in danger of death when the AE occurs, and it does not mean that the AE may cause death if it becomes more severe.

- Permanent or serious disability or loss of function

AE results may cause serious inconvenience or interference to the normal life and activities of subjects.

- Hospitalization required or hospitalization extended

Due to an AE, the subject has to be hospitalized or his/her hospitalization is prolonged regardless he/she was already to be discharged; It is necessary to clarify that this condition is caused by adverse events, rather than elective operation, non-medical reasons, etc.

- Congenital abnormality or birth defect

The offspring of the subjects suffer from malformations or congenital functional defects.

- Other significant medical events

Medical and scientific judgment is required for deciding whether to accelerate the report of other situations. Significant medical events may not immediately endanger his/her life, cause death or hospitalization, but they are usually considered as a serious event if medical measures are needed to prevent the occurrence of one of the above situations. For example, important treatment in the emergency room or allergic bronchospasm at home, cachexia or convulsion without hospitalization, drug dependence or addiction, etc.

When it fails to clearly judge whether it is a SAE, the investigator should consult with the Sponsor and the Ethics Committee.

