## 2. Cardioembolic cerebral infarction

(1) It usually occurs abruptly during activity, with immediate peak neurological deficits;

(2) Cranial CT/MRI shows single or multiple scattered lesions involving the cerebral cortex, often exceeding the territory supplied by a single blood vessel, with a tendency of hemorrhagic transformation.

(3) Evidence of source of emboli in heart, or other concomitant organ embolisms may be found.

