#### **4.4.3 Severe Adverse Events**

The differences in the proportions of patients with SAE between treatment groups and their corresponding 95% CIs will be estimated based on Newcombe–Wilson. The ORs and 95% CIs will be estimated with the logistic regression. Chi-squared test or Fisher’s Exact test will be used to compare the number of each SAE combination according to system organ class and preferred term between treatment groups.

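### Stroke progression judged expected is not an adverse event, expected is undefined, and no by-arm comparison of death, intracranial haemorrhage or neurological worsening stands outside AE classification

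*Combined protocol and SAP*

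**What the plan says.** Protocol 7.3.1, in its list of events that are not adverse events, includes "The disease under study, or the expected progress, signs or symptoms of the disease under study". The next sentence limits this: "However, if the severity is beyond the expected level based on the subject's condition, it shall be considered as an AE". Neither document says how the expected level is set, and neither describes adjudication of that judgement.

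Other parts of 7.3.1 point towards recording. The general definition takes in any unintended "symptom or disease (new or worsening) that is chronologically associated with the use of a certain study drug". The list of qualifying events includes "The deterioration of preexisting diseases, including the increase in the frequency and/or severity of the diseases". The seriousness criteria begin with "Result in death" and make no exception for the index stroke. Section 7.3.6 requires any SAE to be reported, related or not.

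The safety outcomes in protocol 2.2.3 are "Incidence of adverse events (AEs) in each group", the incidence of treatment-related events, and changes in vital signs and laboratory data; SAP 2.3 matches. Protocol 8.5 defines three special-interest types: liver impairment, renal impairment and hypokalaemia. SAP 4.4.2 analyses treatment-emergent AEs. SAP 4.4.3 estimates "The differences in the proportions of patients with SAE between treatment groups and their corresponding 95% CIs". Both SAP sections also compare events by system organ class and preferred term.

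**The concern.** Patients enter with an NIHSS of 6 to 20, and worsening of the index stroke is one of the harms a safety review of a stroke drug most needs to see. Under 7.3.1 that worsening counts only if the investigator thinks it exceeds an unstated expectation. Two sites could see the same deterioration on Day 3, record it differently, and both be within the protocol.

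Whatever is not recorded as an AE cannot reach the SAE tables. If those tables are the only between-arm comparison of clinical harm events, a real increase in progression could be diluted and the trial could report no signal without having looked squarely for one.

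**Working it through.** The plan gives no figure on this point. The check is therefore a comparison of the texts, followed by an illustration on assumed rates.

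**Step 1. How each event type is handled**

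| Event | Text pointing to recording | Text pointing away |
|---|---|---|
| Progression of the index stroke, judged expected | General definition covers worsening disease; deterioration of pre-existing disease is listed | Excluded by the specific rule for the disease under study |
| Progression judged worse than expected | The exception in the same bullet | None |
| Death | Listed seriousness criterion; any SAE is reportable | Only if the fatal course is first ruled not to be an adverse event |
| Haemorrhagic transformation | New or worsening disease; protocol 1.1 names it as an adverse reaction of reperfusion therapy | Not named in the exclusion, but abnormal safety evaluations related to underlying disease are also excluded up to an expected level, and Appendix 1 describes cardioembolic lesions "with a tendency of hemorrhagic transformation" |
| Recurrent stroke | New disease | Not naturally read as progress of the index stroke |

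Only the first row is excluded by the text itself. Loss of a death or a haemorrhagic transformation needs a site to treat the exclusion list as overriding the general AE and SAE definitions.

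**Step 2. Is anything captured independently of the AE label?**

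- Outcomes: none of the three events appears in protocol 2.2.3 or SAP 2.3.
- Special-interest events: none is neurological or haemorrhagic.
- SAP 4.4.2 and 4.4.3: the organ-class and preferred-term tables hold only what was first recorded as an AE. SAP 4.4.4 covers vital signs and laboratory values.
- Imaging: CT is scheduled at screening only, and MRI is optional.
- Scales: the first post-baseline NIHSS and mRS are at Day 14, so no scheduled scale captures early worsening as it happens.
- mRS: Appendix 2 scores death as 5, so the Day-90 distribution does not separate death from severe disability. Protocol 8.4 uses 6 for composite-strategy events, which needs separate reconciliation.

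Death does end follow-up under protocol 6.3.3, and SAP 4.2.1 tabulates dropout reasons by arm. The raw information on deaths should therefore largely exist, but no planned table compares it.

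**Step 3. Would under-recording matter?**

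The arm size comes from the plan: 388 / (1 − 0.15) = 456.5, rounded up to 457. The event rates, the doubling in one arm and the half-recording are assumptions, because the documents give none. Half-recording is taken as equal in both arms because classification is blinded. With Δ the difference in recorded rates, p̄ their mean and n = 457,

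power = Φ{[Δ√n − 1.96√(2p̄(1−p̄))] / √(p₁(1−p₁) + p₂(1−p₂))}.

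For 5% against 10%, all recorded: (0.05 × 21.38 − 1.96 × 0.3725) / 0.3708 = 0.91, so power is 82.0%. With half recorded (2.5% against 5%): (0.025 × 21.38 − 1.96 × 0.2687) / 0.2681 = 0.03, so power is 51.2%.

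| Assumed true rates | All recorded | Half recorded |
|---|---|---|
| 2% vs 4% | 42.5% | 23.7% |
| 5% vs 10% | 82.0% | 51.2% |
| 8% vs 16% | 96.2% | 72.2% |

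This shows that under-recording on such a scale would matter. It does not show that it occurred.

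**The case against.** The strongest reply is that the rule is narrower than it looks. Worse-than-expected progression is an AE under the same bullet. Death is a listed SAE criterion, and doubtful SAEs go to the sponsor and the ethics committee. Haemorrhagic transformation and recurrent stroke are not named in the exclusion, and Appendix 1 is a diagnostic excerpt, not guidance on expectedness. The rule on pre-existing disease can be read as general, with the rule on the disease under study governing the stroke. Recorded events are compared by preferred term as well as in total. Harm through worse progression would also tend to show in the primary mRS endpoint and in NIHSS at Days 14, 30 and 90.

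Most of this stands, and it rules out several stronger readings that a reader might infer:

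- **That deaths or haemorrhagic transformation are excluded by definition.** No text says so; it takes a site's misreading.
- **That a stated number of deaths is missing.** Taking 3% to 6% mortality of 457 (14 to 27 deaths) and halving it gives about 7 to 14 per arm, but neither the mortality nor the half comes from the documents.
- **That the rule favours the active arm.** Investigators classify blind. Bias is possible if treatment alters progression, but nothing in the design builds it in.
- **That the AE label moves the primary result.** Withdrawal because of an AE counts as failure, while other withdrawals use the nearest mRS. But protocol 2.3 already counts death as failure, a patient with no post-treatment mRS fails whatever the cause, and a deteriorating patient's last score would usually exceed 1.

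The reply does not supply a criterion for expected or an independent comparison. The efficacy scales are a partial substitute: they begin at Day 14, merge death with severe disability, and do not identify haemorrhage.

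**Conclusion.** The concern holds in limited form. Expected-severity progression is outside the AE definition on an undefined, investigator-judged threshold, and no by-arm comparison of all-cause death, intracranial haemorrhage or neurological worsening is planned independently of that judgement. The likely consequence is under-counting in both arms and reduced sensitivity to important stroke harms. Its size cannot be derived from the documents, and the power figures above rest wholly on assumed rates and assumed half-recording. It is a worthwhile, inexpensive improvement to the plan. It is not evidence that the trial's safety findings are wrong.

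**What to change.** In protocol 7.3.1, state that every death is recorded as an SAE. State also that recurrent stroke, intracranial haemorrhage or haemorrhagic transformation, and neurological worsening from baseline are recorded as AEs whether or not expected, and as SAEs when a seriousness criterion is met. Limit the exclusion to stable signs of the index stroke present at baseline. In SAP 4.4, add by-arm comparisons of all-cause death to Day 90 and of each of these events, using the Newcombe–Wilson intervals already specified there.

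The cost is wording, more SAE forms, and higher reported AE and SAE rates in both arms. No new procedure is needed. Without added imaging, haemorrhage that causes no symptoms would still go undetected.

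The third IDMC minutes record that all 914 patients had finished follow-up and that database lock was agreed, so new wording cannot recover events that sites did not record. What remains practical is an all-cause death table by arm, built from follow-up and dropout records and labelled as added. It should state how many patients have unknown vital status, because protocol 5.7.1 stops most data collection after withdrawal.
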